**Background:**

Deep iron stores in blood donors are a common phenomenon. However, whether iron deficiency has an effect on the health of the donors has not been sufficiently studied. The threshold values for a clinically relevant iron deficiency are very controversial both in general medicine and especially among blood donors. Some poorly controlled studies with oral iron replacement in regular blood donors have shown that the long-term ability and willingness to donate blood could be improved. However, the studies were unable to demonstrate a positive effect on the health of the donors. It is therefore still controversial today whether iron deficiency in regular blood donors should be sought and substituted.

**Aim of the project:**

- Detailed description of the iron deficiency problem in a large group of blood donors.
- Clarification of the link between low iron stores and potentially related complaints, especially fatigue.
- Definition of a lower iron storage limit in blood donors, above which somatic and psychological complaints occur.
- Proof of the effectiveness of intravenous iron substitution and thus formal proof of the connection between iron deficiency and symptoms.
- Proof of the safety of intravenous iron substitution in blood donors.

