**Secondary endpoints:**

- Subjectively perceived change in fatigue after administration of the study drug, measured with a numerical rating scale from -10 to +10
- Improvement in general and mental well-being after intravenous iron replacement, measured by multiple psychometric tests.
- Change in haemoglobin and iron parameters after intravenous iron substitution.
- Tolerance of intravenous iron in healthy blood donors.
- Improvement of fatigue in the following subpopulations: Women, men, ferritin <25, ferritin >25, fatigue scale <4, fatigue scale >4 (see stratification criteria)

The main endpoint "fatigue" should be asked in a colloquial sense without further definition. In an earlier study, the measurement of fatigue using a numerical rating scale or a visual-analogue scale was successfully applied to women with chronic fatigue and reduced body travel^5^. With the help of this endpoint, it was possible to demonstrate a clinically relevant reduction in subjectively perceived fatigue in a statistically significant manner. Since "fatigue" is experienced by different people in very different ways, various subqualities of "fatigue" are also recorded as a secondary endpoint with the help of the Multi-dimensional fatigue symptom inventory, short form (MFSI-SF).^23^

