**4.5.2 Second study visit / study completion**

In order not to blur the effect of iron substitution, no whole blood, red cells, thrombocytes or plasma may be donated from the first blood donation at the screening until the final visit. The second, final visit takes place six to eight weeks after administration of the study drug (allowed time window 42 to 56 days). The participant is asked to complete the questionnaire package for a second time. In addition, the study coordinator will ask about any side effects on the study medication. Blood is then sampled and the blood count and various iron parameters are determined again. The material is frozen at -70° C. The study is now completed for the participant. If she or he wishes, a regular blood donation may be made at the end of the study.

Following this visit, the participant is informed in writing whether he or she has received the iron supplement or the placebo. In addition, the laboratory results of the first visit and the ferritin value of the second visit will be sent to the volunteer.

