**7.2 Definitions**

**(See also Appendix B, page 13)**

**7.2.1. adverse event (AE)**

For the purposes of this protocol, an adverse event (adverse event = AE) is any occurrence or worsening of a symptom, pathological finding or medical condition during or after administration of the study drug, regardless of whether a relationship with the study drug is suspected. Side effects are evaluated by means of open questions. If available, more detailed and specific questions follow. A physical examination, special laboratory tests or other tests for detection are not routinely performed and are only ordered if the severity or nature of the condition medically requires it.

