**8. Power analysis and statistics**

The main endpoint of the intervention study is the difference in the mean level of fatigue on the numerical rating scale between the ferinject and placebo groups four to six weeks after infusion of the study drug. Based on empirical values from the literature, a standard deviation of the fatigue values of 2.5 points can be assumed. A mean difference of one point on the scale is considered clinically relevant.

200 subjects per group lead to a power of >95% to detect such a reduction with a two-sided α error of 0.05. For a secondary analysis this number of cases leads to a power of about 85% to detect a statistical interaction of the treatment effect with a subgroup in the order of 1.5 points. The primary stratification criterion will be the ferritin value at baseline (<25 µg/l versus ≥25 µg/l). Secondary stratification criteria will be sex and fatigue at baseline (<4 versus ≥4 on the numerical rating scale).

The mean values on the numerical rating scale will be compared by means of covariance analysis between the groups corrected for baseline value of the numerical rating scale. For stratified analyses we will perform an interaction test using least squares regression models. All analyses will be performed according to the intention-to-treat principle, including all randomized patients in the group to which they were initially randomized. Any missing values are replaced by multiple imputation. In a sensitivity analysis only subjects with complete data are included. All P-values are two-sided. The data analysis is performed under blind conditions, i.e. the statistician in charge will not know which of the two groups analysed received iron and which placebo. All analyses are performed in Stata Release 11 (StataCorp, College Station, TX).

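### The Summary's safety aim claims more than about 200 treated donors can show, and the one scheduled side-effect question is late and narrower than the protocol's own adverse event definition

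*Protocol*

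**What the plan says.** Section 1 (Summary, Aim of the project) includes the aim "Proof of the safety of intravenous iron substitution in blood donors". The operative sections are more modest. Section 2.4 says the side-effect spectrum in healthy donors is to be described, Section 3.3.3 asks how the infusion is tolerated, and the secondary endpoint in Section 4.3.2 is "Tolerance of intravenous iron in healthy blood donors".

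Section 8 bases the sample size on the fatigue scale. For the spread it states that "a standard deviation of the fatigue values of 2.5 points can be assumed". The target effect is a 1-point difference between the group means, and the resulting power claim reads "200 subjects per group lead to a power of >95% to detect such a reduction with a two-sided α error of 0.05". It gives no safety rate, margin or hypothesis.

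On collection, Section 7.2.1 counts as an adverse event any new or worsened symptom, finding or condition during or after administration, whether or not the drug is suspected. It then says "Side effects are evaluated by means of open questions", with more specific questions as follow-up and no routine examination or special test to detect events. Section 4.5.2 places the final visit 42 to 56 days after the infusion; there, "the study coordinator will ask about any side effects on the study medication". The infusion itself lasts 15 minutes (Section 4.5.3).

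Other routes are written down. Participants are asked to contact the donor physician if side effects occur (Section 9), all side effects go into the patient documentation and eCRF and are followed up (Section 7.3), and serious events reach the investigator, usually the same day (Section 7.4).

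**The concern.** There are two separate issues.

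**The aim.** A claim of proof needs a stated rate or margin to rule out and enough exposed donors to do so. The protocol has neither. A quiet result in about 200 people could be read as meeting the Summary aim when it settles little about uncommon reactions. The participants are healthy volunteers, and Sections 2.3 and 11.2 expect the results to bear on donation practice.

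**The enquiry.** The reactions named in Section 7.1 (injection site, headache, gastrointestinal, rash) are mostly mild and would be expected soon after the infusion. Asking six to eight weeks later depends on recall. Asking about effects of the medication also invites the participant to judge causality first, which the definition in Section 7.2.1 sets aside. Events not captured near the infusion cannot be recovered in the analysis, and tolerance is a named secondary endpoint.

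**Working it through.** **1. The plan's own figures reproduce.** Inputs from Section 8: 200 per group, SD 2.5, difference 1 point, two-sided α 0.05.
- Main comparison: SE = 2.5 × √(2/200) = 0.25. Power = Φ(1/0.25 − 1.96) = Φ(2.04) = 97.9%, against more than 95% stated.
- Interaction: "this number of cases leads to a power of about 85% to detect a statistical interaction of the treatment effect with a subgroup", for 1.5 points. Assuming equal subgroups, 100 per cell, SE = √(4 × 2.5²/100) = 0.5. Power = Φ(1.5/0.5 − 1.96) = Φ(1.04) = 85.1%.

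The sample size is sound for fatigue. Nothing in it refers to safety.

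**2. What zero events would exclude.** With 1:1 allocation (Section 4.6), about 200 donors receive iron.
- One-sided 95% upper limit: 1 − 0.05^(1/200) = 1.49%.
- Two-sided: 1 − 0.025^(1/200) = 1.83%.
- If 180 are observed (10% loss, assumed; no rate is stated): 1.65% and 2.03%.

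**3. Chance of seeing at least one case, 1 − (1 − p)^200.** The protocol gives no reaction rates, so these are assumed.

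| True rate | Chance of ≥1 case in 200 | Treated donors needed for a 95% chance |
|---|---|---|
| 1 in 100 | 87% | 299 |
| 1 in 200 | 63% | 598 |
| 1 in 1,000 | 18% | 2,995 |
| 1 in 10,000 | 2% | 29,956 |

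Section 7.1 itself describes anaphylaxis as very rare, so it lies beyond what 200 exposures can assess.

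**4. Comparing the arms** (200 per arm, two-sided 0.05, assumed rates). Power is 37% for 2% v 5%, 48% for 5% v 10%, and 80% for 10% v 20%. By Fisher's exact test, 5 v 0 events gives p = 0.061 and 6 v 0 gives p = 0.030. Large differences in common reactions are detectable; moderate ones may well be missed.

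**5. Effect of incomplete recall.** If a fraction f of events is recalled equally in both arms, the observed difference is f × p₁ − f × p₀ = f(p₁ − p₀). The placebo arm protects the direction of the comparison but not its size. As an illustration only, f = 0.5 turns 10% v 20% into 5% v 10%, and the power in step 4 falls from 80% to 48%. The documents give no figure for f.

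**6. Enquiry against definition.** Section 7.2.1 covers any event regardless of suspected cause. Section 4.5.2 asks about side effects of the medication. For the infusion itself, Section 13.2 has the Clinical Investigation Unit (CIU) nurse note only that an infusion could not be given. The protocol text schedules no record of reactions at that point.

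Timing here follows the visit window in Section 4.5.2. Sections 4.3.2 and 8 place the fatigue endpoint at four to six weeks after infusion, and those passages need to be reconciled.

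**The case against.** The strongest reply is that the overstatement is confined to one Summary bullet. Sections 2.4, 3.3.3 and 4.3.2 are descriptive, Section 8 has no rule that turns few events into proof, and Section 10.2 asks for an unbiased and objective final report. A reader might infer that the trial would declare safety proven if few events were reported. The documents do not say so, and the point stands only as a mismatch between aim and design.

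A reader might also infer that side effects are collected once and in no other way. That is too strong. Sections 7.3, 7.4 and 9 give other routes, and a reaction during the infusion would occur in front of the CIU nurse. Appendix B, to which Section 7 refers for definitions, documentation and notification, is not shown and may add more. These routes favour serious or troublesome events, so mild, short-lived reactions remain the weak spot.

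A third tempting reading is that small numbers themselves push the result towards reassurance. They do not: a small sample widens the interval without biasing the rate. Only the late, drug-framed question can lower the count, and that loss cannot be quantified from the documents.

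Finally, open and non-leading questions with follow-up are a legitimate choice. That stands. The objection here is to when the question is asked and what it covers, not to its being open.

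**Conclusion.** The concern holds in limited form, and the change should be made. The Summary aim claims a property the design lacks: zero events in about 200 treated donors leaves a true rate of up to about 1.5% (one-sided) or 1.8% (two-sided) possible, and slightly more with dropout. These limits assume about 200 treated and fully observed donors. The detection and power figures also rest on assumed reaction rates. The enquiry point is smaller. The visit-2 question is narrower than the protocol's own definition and probably under-counts brief, mild reactions, by an unknown amount and subject to what Appendix B contains. The sample size and power for fatigue are unaffected.

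**What to change.** 1. **Aim.** In the Summary, replace the proof-of-safety aim with a description of tolerability, in line with Sections 2.4, 3.3.3 and 4.3.2, and add that rare reactions cannot be excluded with this number of donors.
2. **Visit-2 question.** Align Section 4.5.2 with Section 7.2.1 by asking about any new or worsened symptom since the infusion, with its onset date, in both arms. Ask it only after the fatigue scale and the other questionnaires are complete, so that it cannot prompt guesses about allocation before the primary outcome is scored.
3. **End-of-infusion record.** Have blinded staff already present (the study assistant or donation-centre staff) record any reaction in both arms. The CIU nurse should not do this, because she randomises, prepares and gives the infusion and so knows the allocation (Section 4.6).

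Check Appendix B first, in case it already covers items 2 or 3. How the event rates and their intervals are presented can be left to the analysis plan.

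The cost is wording, one reworded question and a small recording burden, with no extra visit and no change in sample size. Background reports will rise slightly in both arms, which the placebo arm controls.

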**Study design:**

- Descriptive survey in a large collective of blood donors to determine the iron status and associated symptoms
- Double-blind, randomized, placebo-controlled interventional study with intravenous administration of iron carboxymaltose (Ferinject®) or placebo in healthy blood donors with reduced to low normal iron stores

**Primary endpoint of the intervention study:**

Improvement in subjectively perceived fatigue after intravenous iron supplementation in randomized, double-blind comparison with placebo

**Main inclusion criteria of the intervention study:**

Blood donor suitability, serum ferritin ≤50.0 μg/l

**Main exclusion criteria of the intervention study:**

Anemia, intravenous iron intolerance, previous anaphylactic response, active diseases, known iron overload, acute or chronic bleeding, body weight <50 kg and >85 kg (women) / >100 kg (men), age <18 or >65 years

**2. Background and current state of knowledge**

**2.1. Iron: Physiological aspects**

The human body contains about 3 to 4.5 grams of iron, depending on sex and size. Most of this is found as haem-bound iron in the erythrocytes^1^. One gram of haemoglobin contains 3.4 mg iron. This shows that a whole blood donation of 450 ml removes between 180 and 250 mg iron from the body. In addition to its vital role as an oxygen carrier in the red blood pigment, iron is also responsible for numerous essential functions in many other proteins and enzymes. The basis of this important biological role is the high redox potential of iron. However, the potentially toxic properties of excess iron in the body are also based on the same mechanism, as increased radical formation can lead to damage to various organs. The distribution of iron in the organism is therefore well regulated. In the short term, excess iron is absorbed by macrophages of the reticuloendothelial system. In the long term, iron is stored in the cells mainly as a macro-complex with the protein ferritin. Serum ferritin therefore reflects the body's storage iron and serves in medicine as the most important laboratory parameter for the diagnosis of iron deficiency.

**2.2 Iron deficiency without anaemia**

The full picture of a severe iron deficiency is unmistakable with all the effects of anaemia such as paleness, weakness, exhaustion, tiredness and many other symptoms. Much more difficult to classify are mild iron deficiency conditions that have not yet led to anaemia. This topic is still highly controversial in internal medicine. Many different symptoms such as chronic fatigue, concentration disorders, exhaustion, depression or lack of drive are attributed to this constellation. Since iron plays a central role in many essential enzymes, for example in the muscles and the brain, such complaints can be explained theoretically well.

Clinical studies provide certain indications that iron deficiency without anaemia actually leads to symptoms. For example, after six weeks of oral iron supplementation in non-anaemic women with laboratory iron deficiency under endurance training, a significantly higher increase in aerobic capacity was demonstrated^2^. In adolescent US women with iron deficiency without anaemia, eight weeks of oral iron replacement resulted in significant improvement in various cognitive functions compared to the placebo control group^3^. In another study, dietary iron supplementation led to a general improvement in various health characteristics^4^. In an important study from the University Hospital of Lausanne, women with latent iron deficiency who suffered from unexplained fatigue were treated with placebo-controlled peroral iron. Using a numerical rating scale, a significant improvement in fatigue was shown^5^. However, this study is controversial, as due to peroral iron substitution with black discolouration of the stool and gastrointestinal complaints, the verum and the placebo could not be administered really blindly and a placebo effect could therefore not be reliably excluded.

Complaints caused by iron deficiency without anaemia are generally mild and unspecific. They can easily be confused with symptoms of other diseases or everyday ailments. It is often difficult for the doctor to decide whether

a postulated iron deficiency is actually responsible for the patient's symptoms. The condition of iron deficiency without anaemia has been propagated in recent years, especially by the pharmaceutical industry, as an independent clinical picture. Self-proclaimed iron experts in specialised medical practices ("iron centres") have also taken up the subject and practise generous intravenous iron substitution. Reports in the lay press have caused considerable unrest in broad sections of the population^6^.

The scientific evidence for generous iron substitution in iron deficiency without anaemia is insufficient. By promoting high iron limits and frequent iron infusions, negative health consequences cannot be ruled out for a large number of people. Based on the current data, it is unclear above which limit value of the iron parameters a clinically relevant iron deficiency can be excluded and no iron substitution is indicated.

**2.3 Iron deficiency in blood donation**

In blood donors, deep iron stores are a well-known phenomenon^7^. It is generally accepted that repeated donations cause or aggravate iron deficiency^8^. A pooled analysis^7^ of four studies^9-12^ found an average ferritin of 124 μg/l in first-time male donors and 47μg/l in repeat male donors. In women, the corresponding ferritin values were 46 μg/l and 25 μg/l. The development of an iron deficiency seems to depend not so much on the total number of donations, but on their frequency over time^10,13^. Data from the Zurich blood donor service SRK for long-term blood donors also showed that the iron balance stabilises in the long term with very frequent donations^14^. A study with so-called super donors (13 donations per 2 years)^15^ proves that the organism is able to massively increase the absorption of iron from the intestine during frequent blood donations. Hepcidin, which prevents enteral iron absorption, was significantly reduced in these subjects. Similar results are also reported by the Zurich blood donation service SRK^16^.

Most data on iron status in blood donors come from small, poorly controlled studies and are sometimes contradictory. In an early study from Albuquerque, NM, with 1021 unselected blood donors, serum ferritin of less than 12 μg/l^10^ was found in 23.4% of the women and 7.7% of the men. In a Norwegian study 21.7% of the female and 4.6% of the male new donors were already anaemic (haemoglobin below the donor threshold)^17^. 56.9% of these women had ferritin <30 μg/l and 20% <15 μg/l. Only in 3.3% of these men the ferritin was <30 μg/l and only in one below 15 μg/l^17^. For Switzerland, there are data published as posters from the Zurich blood donation service SRK^18^: In 1,539 donors younger than 40 years, 25.9% had ferritin below 15 μg/l. This was the case in 51.7% of women and 4.7% of men. Interestingly, even in 25.1% of healthy new donors the ferritin was less than 15 μg/l.

In the field of blood donation, it is also unclear today whether iron depletion actually has health effects. It can be proven that peroral iron substitution can keep the total body iron constant in men who frequently donate blood and even slowly increase it in women^19^. It has also been shown that peroral iron substitution can improve the ability to donate and prevent donor loss^20,21^ but there is no clear evidence that iron deficiency in blood donors really correlates with symptoms and

iron substitution can reduce complaints or adverse health outcomes. Finally, it is unclear above which lower ferritin limit iron deficiency becomes symptomatic and must be treated. Should it actually be proven that empty iron stores have a negative effect on the health of the donors, this would have direct consequences for blood donation practice. Regular monitoring of iron stores should be declared mandatory and, if necessary, longer donation intervals or regular iron replacement should be introduced.

**2.4 Study medication**

Iron carboxymaltose (Ferinject®) has been approved in Switzerland for intravenous iron replacement by Swissmedic since 2008 and is subject to health insurance contributions. The indication is for laboratory-proven iron deficiency conditions that do not respond to oral iron substitution or for which oral substitution is contraindicated for medical reasons. In the present study, only subjects are included in whom iron deficiency is very likely to occur with a ferritin ≤50 μg/l. As discussed in chapter 3.1, parenteral administration must be preferred to oral iron substitution for technical study reasons. The use of Ferinject® is intended for the pathophysiological study of the not yet fully understood phenomenon of iron deficiency without anaemia. Therefore, only the endpoints specific to the study will be assessed in terms of response. In addition, the spectrum of side effects of Ferinject® in healthy blood donors will be described.

The iron carboxymaltose infusion will be used to replenish iron stores. There is no additional iron deficit due to haemoglobin-bound iron in our volunteers. Roughly estimated, the iron stores in a woman are 500 mg and in a man 1000 mg of iron. A unit dose of 800 mg iron carboxymaltose was chosen for the study. This dose guarantees a sufficient filling of the iron stores in both sexes and in light and heavy persons. At the same time, the chosen dose should not increase the ferritin in equilibrium above the upper laboratory norm in any subject. Thus, long-term toxicity due to iron overload is not to be feared.

